## Abstract

**Background:**

The prevention of internalizing and externalizing behavioral problems in children is a critical scientific and public health priority. Research highlights maternal sensitivity—defined as a caregiver’s ability to perceive, interpret, and respond appropriately to their child’s cues—and consistent but non-coercive discipline as key factors in reducing these behavioral issues. The Video-feedback Intervention to Promote Positive Parenting and Sensitive Discipline (VIPP-SD) aims to enhance maternal sensitivity and promote non-coercive discipline strategies. Meta-analyses have demonstrated its effectiveness in improving parental sensitivity, limit-setting practices, and child attachment security, particularly among socioeconomically disadvantaged families. However, evidence on its impact on externalizing behaviors remains mixed, with some studies suggesting delayed or context-specific effects. This project aims to evaluate VIPP-SD’s impact on parental sensitivity, discipline, child behavioral problems, and parental mental health in Portugal. Additionally, it seeks to assess the intervention’s cost-effectiveness by analyzing health outcomes, resource utilization, and associated costs.

**Methods:**

The program consists of a baseline visit, four intervention sessions, and optional booster sessions, focusing on themes such as sensitive responsiveness, positive reinforcement, and empathetic boundary-setting. 120 families from vulnerable populations in Portugal will be recruited and randomly assigned to the VIPP-SD intervention or the same number of contacts without feedback on parenting. Trained interveners will deliver the intervention. Pre- and posttest assessments include observed and self-reported parenting behaviors, parental mental health, quality of life, and resource use. Follow-up assessments include questionnaires on parent and child variables.

**Discussion:**

The study aims to provide robust evidence to inform health policy decisions and prioritize cost-effective early interventions that improve developmental outcomes, reduce societal costs, and support family well-being.

**Trial registration:**

NCT07153198, 02/09/2025.

**Supplementary Information:**

The online version contains supplementary material available at 10.1186/s40359-025-03431-3.

Given the high prevalence of internalizing and externalizing behavioral problems among youth, their prevention represents an important scientific and public health priority [3, 34]. Empirical evidence indicates that increasing maternal sensitivity—defined as a caregiver’s ability to perceive, interpret, and respond appropriately to their child’s cues—may be an effective strategy for reducing the incidence and severity of these behavioral problems over time [8, 13, 27]. Therefore, interventions aimed at enhancing maternal sensitivity could play a crucial role in promoting better developmental outcomes and mitigating future behavioral difficulties in children.

In addition to its potential to improve developmental outcomes, the prevention of internalizing and externalizing behavioral problems may also yield significant economic benefits. By reducing the incidence and severity of these issues through interventions that increase maternal sensitivity, it is possible to decrease the long-term costs associated with mental health services, educational support, and other related resources. Thus, investing in preventive strategies not only supports the well-being of children and families but may also contribute to substantial savings in healthcare and social service expenditures in the future [32]. In line with Heckman’s research, which shows that investments in early childhood education provide higher economic returns compared to later-stage interventions, such investments increase productivity, reduce social costs, and help alleviate social inequality by giving disadvantaged children a better start [16].

## VIPP-SD

The Video-feedback Intervention to Promote Positive Parenting and Sensitive Discipline (VIPP-SD) is an attachment- and social learning-based intervention aimed at promoting parental sensitivity and the use of developmentally appropriate, non-coercive discipline strategies [18]. The VIPP-SD intervention integrates the enhancement of parental sensitive responsiveness [2] with parent coaching focusing at preventing coercive parent-child interaction cycles [24] and facilitating sensitive limit-setting practices. VIPP-SD consists of a baseline visit and four intervention sessions (with the option of one or two additional booster sessions), held weekly or biweekly, depending on the family's needs and availability. A previous meta-analysis revealed that intensive interventions with numerous sessions often revealed negative effect sizes, in contrast with shorter and more focused interventions [5].

The VIPP-SD approach aims at strengthening parenting skills and promoting a sensitive and responsive caregiving environment, fostering secure parents-child attachment and better socio-emotional outcomes, with a lower likelihood of long-term behavioral problems. Specifically, VIPP-SD addresses disciplinary strategies alongside sensitivity themes through: (1) the differentiation between attachment and exploration behaviors; interpretation of child's behavior and significance of a sensitive response to it; and the importance of sharing emotions; (2) the application of distraction and induction as non-coercive techniques in response to challenging child behaviors or conflict-prone situations; (3) the utilization of positive reinforcement, whereby parents praise adaptive behaviors and ignore maladaptive, attention-seeking actions; (4) the implementation of a sensitive interaction pause to de-escalate conflict or temper tantrums; and (5) the demonstration of empathy towards the child in conjunction with consistent disciplinary approaches and explicit boundary-setting [18]. Two booster sessions are meant to reinforce and consolidate all intervention themes.

Developed and tested for over 30 years with more than 2,000 families in 25 RCTs, VIPP-SD [18, 38] has been found to substantially reduce the prevalence of insecure and disorganized attachment in early childhood and is associated with lower levels of externalizing behavior problems in children in several recent studies [23, 31]. A recent meta-analysis [38] concluded that the VIPP-SD intervention had significant positive effects on parenting behavior and attitudes, promoting parental sensitivity and limit setting across various groups, regardless of psychological status. Through increased parental sensitivity and discipline, the intervention was found to improve child attachment security. No overall significant effect was found on reducing child externalizing behavior, although some studies suggest effects may appear over time or in specific contexts. The largest, most robust pragmatic trial to date found a positive effect on externalizing behaviors for at-risk children [23].

In Portugal, a prior randomized controlled trial was performed with socioeconomically disadvantaged families who struggled with multiple stress factors. VIPP-SD was effective in enhancing positive parent-child interactions and positive family relations [22]. The findings also revealed that the VIPP-SD program was successful in reducing maternal harsh discipline among mothers who initially reported high levels of parenting stress. These results underscore the program’s potential to enhance parenting practices in families that are more vulnerable to harsh discipline and child maltreatment [25]. Contemporary science recognizes the importance of replication studies. This project builds on previous work by incorporating measures of sensitivity, parental anxiety and depression, and in addition aims to demonstrate the economic impact of intervening in early relational experiences.

The main objective of the present project is to evaluate whether the VIPP-SD program contributes to enhancing parental sensitivity and promoting the adoption of sensitive discipline parenting practices, with the ultimate goal of reducing behavioral problems in children and improving parental mental health outcomes. Furthermore, the study aims to assess the costs and cost-effectiveness of the VIPP-SD intervention. By analyzing its impact on health outcomes, resource utilization, and associated costs, this research seeks to highlight the potential economic advantages of early intervention. The findings may provide critical evidence to support health policy decision-makers in prioritizing cost-effective preventive strategies for early intervention.

### Objectives and hypotheses

The primary objective of the current project is to examine the effect of the VIPP-SD on parental sensitivity and sensitive discipline of the target parent, from baseline to 8 weeks after and 6 months after the intervention. We expect a statistically significant increase in sensitivity and sensitive discipline among parents from the intervention condition (VIPP-SD) when compared with parents from control condition ("dummy" contacts with interveners) from pre- to post-intervention.The secondary aim of the study is to examine the value of the intervention in reducing children’s behavioral problems, as a function of increased parental sensitivity and the use of sensitive discipline strategies. It is expected that improvements in parental sensitivity and sensitive discipline resulting from the VIPP-SD intervention will be associated with lower levels of behavioral difficulties in intervention group children when compared with children from control condition ("dummy" contacts with interveners) from pre- to post-intervention and follow-up intervention.A third objective is to evaluate the effects of the VIPP-SD on parent-reported parenting practices, parental anxiety and depression symptoms, and parental health related quality of life. We expect that parents in the intervention condition will report a decrease in depression and anxiety symptoms, as well as more nurturing and less restrictive parenting practices from pre- to post-intervention and 6-months follow-up.The fourth objective is to examine the cost-effectiveness of the intervention by assessing the differential impact of the intervention compared to the control on quality adjusted life years (QALY) and resource use and related costs. We expect that VIPP-SD leads to improved health related quality of life (HRQoL) and a reduction in the use of societal resources compared to the control condition.

## Methods

### Recruitment

One hundred and twenty families will be recruited from families attending Family Support and Parental Counseling Centers (CAFAP) and Child Psychology Centers in the Metropolitan area of Lisbon. CAFAP is a specialized social response aimed at supporting families with children and adolescents who are in situations of vulnerability, risk, or danger. CAFAP operates through referrals from entities such as Child and Youth Protection Commissions (CPCJ), schools, health services, or social security, with all interventions conducted in agreement with the legal guardians.

A minimum of 60 families in each condition will participate in the study, with an equal balance (through stratified randomization) of boys and girls. Inclusion criteria for parents will be: (1) fluency in Portuguese, (2) having a child between the ages of 2 and 6 years, and (3) absence of any diagnosed psychopathology, chronic or hereditary illnesses. Parents of children with a known diagnosis of disabilities, chronic or hereditary illnesses will be excluded from the study, since they are eligible for other intervention programs that are targeted to their specific needs. The expected completion date for participant recruitment is July 31, 2026.

We conducted a Power Analysis to ensure sufficient statistical power, based on previous VIPP studies. Expected effect size for primary outcome is meta-analytically *f* = 0.18 [38]. Assuming *f* = .18, power = .90, and *α* = .05, and correlation between pretest and posttest of *r* = .35, at least 54 participants per group are required. To account for attrition, we set a target of 60 per group.

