### Data analysis

Data inspection procedures will be performed once the data collection is completed, but prior to the commencement of formal statistical analyses. These preliminary analyses will focus on examining the quality and integrity of the data collected, identifying any potential errors, outliers, or inconsistencies. Data validation steps will include checking for missing values, verifying the distribution of key variables, and ensuring adherence to predefined inclusion criteria. The results of this inspection will guide decisions on data cleaning, imputation, or any necessary adjustments before proceeding with more advanced statistical methods.

For all study objectives, the impact of the VIPP-SD intervention will be compared to the control condition using intent-to-treat (ITT) analyses. To assess the intervention's effect in the key outcomes, including parental sensitivity and sensitive discipline, child behavior problems (SDQ), depression, anxiety, and stress (DASS-21) and child rearing practices (CRPR-Q), we propose the use of a repeated measure ANOVA. In this model, experimental condition will be treated as a between-subjects factor, and assessment time-point as a within-subjects factor. The regression coefficient for the interaction between condition and assessment time will estimate differential changes in parental sensitivity and sensitive discipline between the intervention and control groups over time.

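### The 90% power with 54 per group is power for a 0.72 SD difference in change; the protocol does not say what its f = .18 measures, and if it is the usual two-group f (d = 0.36) power is about 37%

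*Protocol article*

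**What the plan says.** The power analysis is in the Recruitment section of the protocol article. On the effect size it says "Expected effect size for primary outcome is meta-analytically" f = 0.18, citing a meta-analysis of the programme. The other inputs are "Assuming *f* = .18, power = .90, and *α* = .05" and a "correlation between pretest and posttest of *r* = .35". From these it concludes that "at least 54 participants per group are required", and it adds "To account for attrition, we set a target of 60 per group".

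The Instruments section has the observed parenting measures, which carry the primary objective, taken twice: at baseline and at posttest. For the test, the Data analysis section says "we propose the use of a repeated measure ANOVA", with condition between subjects and time within subjects. The condition by time interaction is to estimate the differential change between the arms.

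Nowhere does the article give a standardised mean difference, a raw difference in scale points, or the contrast and SD to which f refers.

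**The concern.** Cohen's f is not one quantity. For a comparison of two group means it equals half the standardised difference. For the interaction in a two-by-two repeated-measures design it equals a quarter of the standardised difference in change. The same .18 therefore means 0.36 SD on the first scale and 0.72 SD on the second.

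The protocol presents .18 as a pooled effect from earlier trials. Such an effect is commonly a between-group difference, yet the figure goes into a calculation that reads it on the interaction scale. If the two scales were mixed, the calculation assumes twice the effect that the source supports. The 90% would then describe an effect larger than the one expected, and anyone judging a non-significant primary result would credit the trial with far more power than it had.

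**Working it through.** **Inputs.** From the Recruitment section: f = .18, alpha = .05, power = .90, r = .35, 54 per group (N = 108), target 60 per group (N = 120). From the Instruments section: m = 2 time points for the observed outcomes. From the Data analysis section: the condition by time interaction is tested. Sidedness is not stated. The F test is used, which is equivalent to a two-sided t test.

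**Step 1: reproduce the plan's figure.** For the within-between interaction, λ = f²·N·m/(1 − r), with 1 and N − 2 degrees of freedom.
- N = 108: λ = .18² × 108 × 2/.65 = 10.77, power .902.
- N = 106: λ = .18² × 106 × 2/.65 = 10.57, power .896.

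The smallest equal group size that reaches 90% is 54, as stated. Other readings tried do not return 54. With three time points the power at N = 108 is .956, so fewer would be needed. The between-subjects main effect gives .62, and .18 as a plain two-group f (λ = f²·N) gives .46.

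**Step 2: what f = .18 means in that formula.** Let the four cell means be 0 and 0 in the control arm, and 0 and D in the intervention arm, in units of the within-cell SD. Each cell's interaction effect is ±D/4, so f = D/4 and D = 4 × .18 = 0.72 SD.

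Check on change scores: their variance is 2(1 − .35) = 1.30, and λ = D²·(N/4)/1.30 = .72² × 27/1.30 = 10.77. This is the same λ and the same power of .902.

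**Step 3: power if .18 is a two-group f.** Assume d = 2 × .18 = 0.36 in raw SD units. The interaction f is then 0.36/4 = .09.
- 54 per arm: λ = .36² × 27/1.30 = 2.69, power .369.
- 60 per arm: λ = .36² × 30/1.30 = 2.99, power .403.
- For 90% power about 212 per arm would be needed: λ = .36² × 106/1.30 = 10.57, power .900.

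**Step 4: sensitivity, with d = 0.36 and 54 per arm.** With a raw-SD standardiser, λ = 3.4992/(2(1 − r)), where 3.4992 = .36² × 27.

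| Reading | λ | Power |
|---|---|---|
| r = .20 | 2.19 | 31% |
| r = .35 (the plan's value) | 2.69 | 37% |
| r = .50 | 3.50 | 46% |
| r = .65 | 5.00 | 60% |
| r = .70 | 5.83 | 67% |
| d standardised by the change-score SD | 3.50 | 46% |

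With 60 per arm the last row becomes 50%. A one-sided test at r = .35 would give 49% at 54 per arm.

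**The case against.** A reader might infer that the sponsor made an arithmetic error, or that the trial has been shown to be underpowered for its expected effect. The documents support neither.

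The number 54 follows exactly from the stated inputs, and the formula behind it matches the planned test and the two observation points. The calculation and the analysis agree with each other.

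The premise that .18 is a two-group f lies outside the article. The article says only that the value is meta-analytic. A meta-analysis can also pool differences in pre-post change, and if the source value is already an interaction f on the raw SD scale, the 90% stands. The plan states f = .18 and never d = 0.36, so the 37% can only be a conditional figure. It also depends on r, on the standardiser and on 54 families being analysed; at r = .65 it is 60%.

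All of that stands, and it sets the form of the point. It does not remove it. None of the two-group readings checked comes near 90%, and on the reading that rescues the figure the protocol still omits that it is counting on 0.72 SD.

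It is also fair to say that power under a baseline-adjusted analysis has no bearing on the figure as it stands, because the article does not plan that analysis.

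**Conclusion.** The point holds in conditional form. It concerns the undefined scale of an input. The arithmetic is sound.

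What is certain: 54 per arm with r = .35 gives 90% power for a difference in change of 0.72 SD, and the article does not say so.

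What is conditional: if the meta-analytic .18 is the usual two-group f (d = 0.36 in raw SD units), the planned test has about 37% power with 54 analysed per arm and about 40% with 60. Across r from .20 to .70 the range at 54 per arm is 31% to 67%, and with a change-score standardiser power is 46%.

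The power statement should be corrected or justified before results are known, because it is the sole printed justification of the sample size.

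**What to change.** Keep the 120 families. Check in the cited meta-analysis which contrast and which SD the .18 refers to, then restate the power paragraph.

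- In either case write: *With 54 analysed per arm and r = .35 the trial has 90% power for a differential change of 0.72 SD.*
- If .18 is a between-group f, add: *For d = 0.36 power is about 37% (40% with 60 per arm).*
- If .18 is an interaction f, say that it equals a 0.72 SD difference in change and show the derivation from the source.

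Power under a baseline-adjusted analysis (about 51% at 54 and 55% at 60 per arm for d = 0.36 and r = .35) belongs in the text only if that analysis is adopted.

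The cost is one paragraph and a look at the source. No extra families or measurements are needed. If .18 is a between-group f, the price is a less favourable power statement.

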### Intervention

In the present study, the VIPP-SD protocol will be implemented using a culturally adapted and linguistically validated Portuguese version [21]. All materials were translated into Portuguese, using the committee approach outlined by [6]. This method involved multiple bilingual translators to ensure the accuracy and cultural relevance of the content. Additionally, all intervention practitioners were trained and will be supervised by certified VIPP-SD trainers, ensuring that they met the standards required for effective implementation of the intervention.

All intervention practitioners participating in the study received formal training in the VIPP-SD protocol. The training was conducted by certified VIPP-SD professionals and adhered to the official guidelines to ensure consistency and fidelity to the intervention model.

To ensure fidelity, intervention feedback scripts will be coded for content based on the guidelines outlined in a coding fidelity manual. To support this process, random sessions will be videotaped or audiotaped for review.

### Study design

To evaluate the intervention’s effectiveness, we will conduct a two-arm randomized controlled trial (RCT) in which participating families will be randomly assigned to either an intervention group or a control group ("dummy" contacts with interveners) after the baseline visit. Parents in the Control Group will receive, at the same frequency as the Intervention Group’s sessions, a phone call addressing topics related to child development (e.g., sleep, nutrition, etc., but not providing feedback on parenting). The protocols will be specifically designed to encourage participants to talk about their children. Randomization will be performed using a computer-generated random allocation sequence, stratified by child age and sex to ensure balanced group characteristics and group assignment will be done after the baseline assessment is completed to minimize potential bias (Fig. 1).

**Fig. 1 Fig1:**

Schedule of the design, sessions, and assessments

### Instruments

Data collection for sociodemographic variables will take place at baseline (pretest). Parental sensitivity and sensitive discipline will be coded from videotaped mother–child interactions by independent, trained observers who are blinded to intervention conditions; these measures will be collected at baseline and immediately post-intervention (posttest). All other measures will be collected at three time points: baseline, posttest, and follow-up. Due to time and personnel limitations, the follow-up evaluation will rely solely on questionnaires.

#### Parental sensitivity and sensitive discipline (observation)

Parental sensitivity will be assessed using the the revised Erickson 7-point rating scales for Supportive Presence (from 1 = *parent completely fails to be supportive to the child* to 7 = *parent skilfully provides support throughout the session*) and Intrusiveness (from 1 = *parent allows the child sufficient time to explore and to attempt to solve tools on her/his own* to 7 = *parent is highly intrusive; her agenda clearly has precedence over the child’s wishes*; [7]. These scales are age-adequate adaptations of the Ainsworth Maternal Behavior Scales [2], which are widely regarded as a gold standard for evaluating the sensitive responsiveness of parents to their children's cues. Supportive presence is defined as the consistent emotional, physical, and psychological availability of a mother, characterized by both verbal expressions and nonverbal behaviors. High sensitivity is associated with positive developmental outcomes in children, including secure attachment and better emotional regulation. Intrusiveness reflects the extent to which a parent disregards or interferes with the child’s autonomy, wishes, interests, or behaviors. The scale captures behaviors that may disrupt the child’s ability to express themselves or make independent decisions. Intrusiveness is often characterized by over-controlling or overly directive parenting, and it can negatively impact the child’s development, particularly their sense of autonomy and emotional well-being. Both sensitivity and intrusiveness are crucial dimensions of the parent-child interaction and provide valuable insights into the quality of the parenting style.

Parental discipline will be observed during a compliance task that tends to elicit challenging child behavior. Three scales will be coded: Positive Limit-Setting, using the revised Erickson 7-point rating scales for Supportive Presence (from 1 = *parent completely fails to provide positive limit-setting*, to 7 = *parent skillfully provides positive limit-setting*; [7], Physical Interference, rated on a 5-point scale (from 1 = *parent does not interfere physically*, to 5 = *parent often interferes physically*; [39], and Laxness, reflecting inconsistent or lenient approaches to setting and enforcing limits, rated on a 5-point rating scale (from 1 = *no laxness* to 5 = *continuous laxness*; [36].

#### Strengths & Difficulties Questionnaire (SDQ, [12] Portuguese version: Fleitlich et al. 10

This 25-item parent-rated scale evaluates emotional and behavioral problems in children aged 2 to 17 years. The items are rated on a 3-point scale: 0 = "*Not true*," 1 = "*A bit true*," and 2 = "*Very true*." The questionnaire is organized into five subscales: (1) emotional symptoms, (2) conduct problems, (3) hyperactivity, (4) peer problems, and (5) prosocial behavior. The total difficulties score is derived by summing the first four subscales (excluding prosocial behavior), yielding a score ranging from 0 to 40. Studies with Portuguese children have reported internal consistency values ranging from 0.60 to 0.70 for the Parent version [1].

